#### Safety set

The safety analysis will analyze all the patients who used the intervention drug at least once and underwent one safety assessment.

### Adherence and protocol deviations

Adherence is determined by the participants at each visit and according to medication adherence. We will describe the proportion of participants using frequency distributions for both groups. Medication compliance will be calculated and compared between two groups according to the ratio of actual medicine administered and the ideal dose that should be received. The medicine distributed to the patients and the medicine not administered will be recorded every 4 weeks.

Significant protocol violations are those that potentially affect the primary measures, such as receiving protocol prohibited medicine, increasing the safety risk of the participants, and ethical concerns.

## Trial population

### Eligibility criteria

This study includes patients with DKD who had macroalbuminuria, and controlled serum creatinine, blood pressure, and hemoglobin A1c levels (HbA1c). Patients with type 1 diabetes or those who received potassium-sparing diuretics are excluded from the study.

### Case enrollment and completion

The enrollment and the number of completed cases will be summarized for each center. The numbers of enrolled cases and each analyzed dataset will be described. Participants may withdraw from the trial intervention and/or fail to provide follow-up data. In addition, participants may withdraw their consent. We will report these items (Table 1), and the total dropout rate will be compared between the two groups.

**Table 1 Tab1:** Withdrawals

Num	Withdrew at…	Reason to withdraw	Type of withdrawal
1	xx	xx	e.g., withdrew consent
2	xx	xx	e.g., stopped intervention early, provided data at follow-up
…	xx	xx	e.g., stopped intervention early, lost to follow-up
…	xx	xx	e.g., completed intervention, lost to follow-up
*n*	xx	xx	xx

### Baseline characteristics

The baseline characteristics of all participants in both groups will be shown in Table 2. The table will describe the following variables: age, height, weight, BMI, female sex, nationality, heart rate, systolic blood pressure, diastolic blood pressure, mean arterial pressure, respiration rate, drug or constitution allergic history, comorbid conditions, and concomitant treatment. The sample will be described according to the full analysis set. The baseline characteristics will be compared between groups.

**Table 2 Tab2:** Baseline characteristics of participants prior to treatment

Characteristic	SZF, number, central tendency (variability)	Irbesartan, number, central tendency (variability)	All participants, number, central tendency (variability)	***p*** value
	*n* = xx	*n* = xx	*n* = xx	
**Demographics**				
Age (years)^a^	xx (xx)	xx (xx)	xx (xx)	.xx
Height (m)^a^	xx (xx)	xx (xx)	xx (xx)	.xx
Weight (kg)^a^	xx (xx)	xx (xx)	xx (xx)	.xx
BMI (kg/m^2^)^a^	xx (xx)	xx (xx)	xx (xx)	.xx
Female sex (*n*,%)^b^	xx (xx%)	xx (xx%)	xx (xx%)	.xx
Nationality (China, other)^b^	xx (xx%)	xx (xx%)	xx (xx%)	.xx
**Vital signs**				
Heart rate (beats per minute)^a^	xx (xx)	xx (xx)	xx (xx)	.xx
Systolic blood pressure (mmHg)^a^	xx (xx)	xx (xx)	xx (xx)	.xx
Diastolic blood pressure (mmHg)^a^	xx (xx)	xx (xx)	xx (xx)	.xx
Mean arterial pressure (mmHg)^a^	xx (xx)	xx (xx)	xx (xx)	.xx
Respiration rate(breath/min)^a^	xx (xx)	xx (xx)	xx (xx)	.xx
**Drug or constitution allergic history (yes or no)**^**b**^	xx (xx%)	xx (xx%)	xx (xx%)	.xx
**Comorbid conditions (*****n*****%)**				
Diabetic retinopathy^b^	xx (xx%)	xx (xx%)	xx (xx%)	.xx
…				
**Concomitant treatment**				
…^b^	xx(xx%)	xx(xx%)	xx(xx%)	.xx

^a^Number, mean, standard deviation

^b^Number, percentage

## Analysis methods

### Outcome measure analyses

#### Primary outcome analyses

The primary analysis will be conducted in the FAS and PPS. The change in 24-h UP (mg/24 h) is the primary outcome. The distribution and changes of 24-h UP at weeks 0, 4, 8, 12, 16, 20, and 24 of medication will be described. Intra- and inter-group comparisons will be made. The distributions of qualitative judgments of 24-h UP at weeks 4, 8, 12, 16, 20, and 24 will be described and compared between groups. The baseline 24-h UP is essential to assess the progression of UP; therefore, analysis of covariance (ANCOVA) will be performed to analyze the 24-h UP change from baseline to week 24, using baseline 24-h UP as a covariate. Interactions between site and group will also be tested.

Table 3 provides a reference for the qualitative determination of the variation. The efficiency rate will be calculated by summing the rate of clinical control, obvious therapeutic effect, and therapeutic effect (Table 4).

**Table 3 Tab3:** 24-h UP qualitative judgments classification standard

Qualitative judgment	Standard
Clinical control	24-h UP< 0.5 g
Obvious therapeutic effect	24-h UP reduction ≥ 50%
With therapeutic effect	24-h UP reduction ≥ 20%
Invalid	Fail to reach the standards above

**Table 4 Tab4:** Analysis of primary outcome

Time point	SZF, number, mean (SD)	Irbesartan, number, mean (SD)	Mean difference (95% CI)	***p*** value
Visit at	*n* = xx	*n* = xx		
Week 0	xx (xx)	xx (xx)	xx (xx to xx)	.xx
Week 4 ^a^	xx (xx)	xx (xx)	xx (xx to xx)	.xx
Week 8	xx (xx)	xx (xx)	xx (xx to xx)	.xx
Week 12	xx (xx)	xx (xx)	xx (xx to xx)	.xx
Week 16	xx (xx)	xx (xx)	xx (xx to xx)	.xx
Week 20	xx (xx)	xx (xx)	xx (xx to xx)	.xx
Week 24	xx (xx)	xx (xx)	xx (xx to xx)	.xx
Overall SZF effect^b^				.xx

^a,b^*p* values comparing between group differences at visit points post-randomization (a) and over the entire24-week trial (b: primary outcome)

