**Methods:**

This trial is a 24-week, randomized, multicentric, double-blinded, double-dummy clinical trial. A total of 120 patients with DKD will be equally and randomly divided into two groups: SZF+ irbesartan simulator or irbesartan + SZF simulator. The 24-h urinary protein change from baseline to week 24 is the primary outcome measure. The secondary outcome measures include serum creatinine, estimated glomerular filtration rate, urinary albumin excretion rate, improvement in traditional Chinese medicine symptoms, fasting blood glucose, 2-h postprandial plasma glucose, hemoglobin A1c, cholesterol, triglycerides, high density lipoprotein, low density lipoprotein, blood pressure, albumin to creatinine ratio, and the Audit of Diabetes-Dependent Quality of Life 19. Our recruitment began in May 2015; currently, we have recruited 100 participants, with a designed maximum sample size of 120. The interim results were reviewed at *N* = 60, and continuing recruitment was recommended. This statistical analysis plan includes our approach to missing data imputation, primary and secondary outcomes analyses, and safety endpoints.

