## Statistical principles

### Overall principles

After completion of the trial, all the statistical analysis tests will use two-sided tests with a nominal alpha level of 0.05, using the SAS [10, 12]. All confidence interval (CI) reports will be 95% CIs. For each outcome, the null hypothesis is the absence of difference between the intervention groups.

The description of measurement indicators will calculate the mean, standard deviation, median, minimum, maximum, and interquartile range (Q3–Q1). Normal continuous variables will be presented as the mean and standard deviation; non-normally distributed continuous variables will be presented as median with interquartile range. Counting indicators will be presented as the frequency and percentage of each category.

Inter-group comparisons will be performed with independent two-sample *t*-tests (normality, homogeneity of variance) or Wilcoxon rank-sum test (non-normality, heterogeneity of variance). Comparisons within normal and nonnormally distributed groups will be performed using paired *t*-test and paired rank-sum test, respectively. *χ*^2^ test or Fisher’s exact probability will be needed for count metrics, and the Wilcoxon rank-sum test will be used for categorical variables. A generalized linear mixed model analysis will be performed on the repeated measured outcome.

In situations where an imbalance in the baseline indicators exists, an adjustment will be required for the efficacy comparison of variables, such as age, sex, and concomitant treatment. The covariance method will be used for continuous variables, and logistic regression analysis was used for count metrics and hierarchical metrics.

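### The text makes the week-24 change in 24-h urinary protein the primary outcome, but the Table 4 footnote gives that label to the overall effect across 24 weeks

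*Protocol article*

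**What the plan says.** The Protocol article gives the primary outcome in three places.

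- **Abstract, Methods:** "The 24-h urinary protein change from baseline to week 24 is the primary outcome measure".
- **Primary outcome analyses, text:** "The change in 24-h UP (mg/24 h) is the primary outcome", with no time point in that sentence. The paragraph then fixes the time point and method: "analysis of covariance (ANCOVA) will be performed to analyze the 24-h UP change from baseline to week 24", with the baseline value as covariate.
- **Primary outcome analyses, Table 4 footnote:** the table lists weeks 0 to 24 by visit and ends with a row named Overall SZF effect, which holds only a p-value. Note (a) covers the post-randomization visit comparisons. Note (b) covers the comparison "over the entire24-week trial (b: primary outcome").

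Two further statements bear on the point. Overall principles says, for repeated outcomes in general, "A generalized linear mixed model analysis will be performed on the repeated measured outcome". On populations, Primary outcome analyses says "The primary analysis will be conducted in the FAS and PPS". Overall principles sets a nominal two-sided alpha of 0.05 for all tests.

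**The concern.** A statistician following the abstract and text would report the week-24 ANCOVA as the trial's primary result. One filling in Table 4 as printed would report the Overall SZF effect p-value. Both could claim to have followed the plan. Table 4 has no row identified as the baseline-adjusted week-24 result, so the analysis described in the text has no evident place in the table meant to report the primary outcome.

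The Discussion part of the abstract says the plan exists to prevent selective outcome reporting and data-driven analysis. It cannot do that while its primary test is stated in two ways. At stake is which number answers the trial's main question, and whether the stated 5% error rate applies to it.

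**Working it through.** **1. The statements side by side.**

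| Place | Quantity called primary | Status of week 24 |
|---|---|---|
| Abstract, Methods | Change, baseline to week 24 | Is the primary time point |
| Primary outcome analyses, text | Change, baseline to week 24, by baseline-adjusted ANCOVA | Is the primary time point |
| Table 4, note (b) | Between-group difference over the whole 24 weeks | One visit comparison under note (a) |

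Table 5 has the same overall row for each secondary outcome shown, and its footnote gives the same explanation without a primary label. The label in Table 4 was therefore put there specifically.

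**2. Why the two quantities can differ.** There are six post-baseline visits (weeks 4, 8, 12, 16, 20, 24). Suppose, for illustration, that the overall effect weights them equally, and let d be a between-group difference.

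- Difference d at weeks 4 to 16, none at weeks 20 and 24: overall = 4d/6 = 0.67d; week 24 = 0.
- Difference d at week 24 only: overall = d/6 = 0.17d; week 24 = d.

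**3. Error rate if either result could be reported as primary.** The plan's own figure is a nominal two-sided 0.05 per test. Let Z1 and Z2 be the two test statistics, standard normal under the null with correlation r. Then

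error = 1 − P(|Z1| ≤ 1.96 and |Z2| ≤ 1.96).

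The correlation r is assumed; the document does not give it. By numerical integration:

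| r | Error |
|---|---|
| 0.9 | 0.0704 |
| 0.8 | 0.0781 |
| 0.7 | 0.0835 |
| 0.6 | 0.0875 |

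**4. Is that range of r reasonable?** For baseline-adjusted week 24 against the baseline-adjusted mean of weeks 4 to 24, r is 0.67 and 0.71 under compound symmetry (correlation 0.5 and 0.7), and 0.76 and 0.84 under AR(1) (0.8 and 0.9 between adjacent visits). These give errors of about 8.5%, 8.3%, 8.0% and 7.6%.

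**5. Simulation under the null.** With 60 per arm, seven visits, 10,000 runs per scenario and the same four correlation structures, one fixed test gave 0.047 to 0.053. Taking either definition within the FAS gave 0.075 to 0.090, consistent with step 3 allowing for simulation error. If the better of FAS and per protocol set (PPS) could also be taken, with 10% to 30% of patients assumed to be left out of the PPS at random, the range was 0.095 to 0.133.

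The sample size of 120 does not enter the argument. The article refers its calculation to the earlier protocol publication.

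**The case against.** The strongest reply is that the weight of the text is one-sided. The abstract names the week-24 change, the analysis section gives its reason for ANCOVA on exactly that change, and only a parenthesis in a table footnote differs. It could be added that the overall row holds a p-value alone and might be the slot intended for the ANCOVA. The first part stands as a guide to what was probably meant, and it shows which way to correct. The second is possible but less likely, because note (b) describes a comparison across the whole trial and Table 5 uses the same row in the same way. Neither removes the conflict, which is between printed statements and so is not something left to a fuller document.

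Three stronger readings are tempting, and the document does not support them.

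- **That the overall effect is known to come from a repeated-measures model.** The mixed-model sentence in Overall principles makes this likely, but nothing links it to Table 4.
- **That the t-test and Wilcoxon rules open further routes to a primary p-value.** Those rules are general, state when each test applies, and are not called primary. The week-24 change has its own specified method.
- **That naming both FAS and PPS itself inflates the error.** Reporting both is usual, and inflation arises only if either may win; if both must succeed there is none. The section on imputation adds the per-protocol analysis as a further step, which hints that the FAS leads. What remains is a missing order, worth a sentence.

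**Conclusion.** The point holds: the plan contradicts itself on which quantity is the primary outcome. This rests on the wording alone and needs no assumption.

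The size is conditional. About 7.0% to 8.8% instead of 5% applies only if the more favourable of the two results could be reported as primary, and it depends on assumed correlations of 0.9 to 0.6. A reader might infer that the trial's error rate is in fact inflated by this amount, or by the larger figures that include the FAS/PPS choice. The document does not support that, because nothing in it says that either result may be picked. The figures show what the ambiguity could cost.

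The choice of deciding population is a secondary clarification, and the main point stands without it.

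**What to change.** Before unblinding:

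1. In Table 4, remove the primary label from note (b) and add a row for the baseline-adjusted ANCOVA of the week-24 change, marked as the single primary result. This agrees with the abstract and the text.
2. Label the Overall SZF effect and the visit-level comparisons supportive, and name the model that produces the overall effect.
3. As a secondary clarification, name the FAS with multiple imputation as the deciding set and the PPS as supportive. This should go together with a correction to the Full analysis set section, which as worded admits only patients who meet the primary objective after treatment. Membership must not depend on post-treatment outcome, or the deciding analysis would rest on a selected set.

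The cost is one footnote, one table row and a short paragraph, plus the reworded FAS definition. No added patients, visits or data collection are needed. The article reports 100 of 120 patients recruited and completion scheduled for June 2022, so at that stage there was time to do this before the final analysis.

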#### Secondary outcome analyses

The secondary outcome of the FAS and PPS will be analyzed, including serum creatinine (SCr, umol/L), eGFR (mL/(min×1.73 m^2^) using CKD-EPI creatinine equation [13]), urinary albumin excretion rate (μg/min), improvement in TCM symptoms, fasting blood glucose (mmol/L), 2-h postprandial plasma glucose (mmol/L), HbA1C (%), cholesterol (mmol/L), triglycerides (mmol/L), high density lipoproteins (mmol/L), low density lipoproteins (mmol/L), blood pressure (mmHg), albumin to creatinine ratio (ACR, mg/g), and the audit of diabetes-dependent quality of life 19 (ADDQoL) [14] The distribution and changes of all the secondary outcomes at the baseline and at each visit point will be compared between and within groups (Table 5).

**Table 5 Tab5:** Secondary outcome analysis

Time point	SZF, number, mean (SD)	Irbesartan, number, mean (SD)	Mean difference (95% CI)	***p*** Value
Scr at	*n* = xx	*n* = xx		
Week 0	xx (xx)	xx (xx)	xx (xx to xx)	.xx
Week 4	xx (xx)	xx (xx)	xx (xx to xx)	.xx
Week 8	xx (xx)	xx (xx)	xx (xx to xx)	.xx
Week 12	xx (xx)	xx (xx)	xx (xx to xx)	.xx
Week 16	xx (xx)	xx (xx)	xx (xx to xx)	.xx
Week 20	xx (xx)	xx (xx)	xx (xx to xx)	.xx
Week 24	xx (xx)	xx (xx)	xx (xx to xx)	.xx
Overall SZF effect ^a^				.xx
eGFR at	*n* = xx	*n* = xx		
Week 0	xx (xx)	xx (xx)	xx (xx to xx)	.xx
Week 4	xx (xx)	xx (xx)	xx (xx to xx)	.xx
Week 8	xx (xx)	xx (xx)	xx (xx to xx)	.xx
Week 12	xx (xx)	xx (xx)	xx (xx to xx)	.xx
Week 16	xx (xx)	xx (xx)	xx (xx to xx)	.xx
Week 20	xx (xx)	xx (xx)	xx (xx to xx)	.xx
Week 24	xx (xx)	xx (xx)	xx (xx to xx)	.xx
Overall SZF effect				.xx
UAER at	*n* = xx	*n* = xx		
Week 0	xx (xx)	xx (xx)	xx (xx to xx)	.xx
Week 4	xx (xx)	xx (xx)	xx (xx to xx)	.xx
Week 8	xx (xx)	xx (xx)	xx (xx to xx)	.xx
Week 12	xx (xx)	xx (xx)	xx (xx to xx)	.xx
Week 16	xx (xx)	xx (xx)	xx (xx to xx)	.xx
Week 20	xx (xx)	xx (xx)	xx (xx to xx)	.xx
Week 24	xx (xx)	xx (xx)	xx (xx to xx)	.xx
Overall SZF effect				.xx
FBG	*n* = xx	*n* = xx		
Week 0	xx (xx)	xx (xx)	xx (xx to xx)	.xx
Week 4	xx (xx)	xx (xx)	xx (xx to xx)	.xx
Week 8	xx (xx)	xx (xx)	xx (xx to xx)	.xx
Week 12	xx (xx)	xx (xx)	xx (xx to xx)	.xx
Week 16	xx (xx)	xx (xx)	xx (xx to xx)	.xx
Week 20	xx (xx)	xx (xx)	xx (xx to xx)	.xx
Week 24	xx (xx)	xx (xx)	xx (xx to xx)	.xx
Overall SZF effect				.xx
2hPG at	*n* = xx	*n* = xx		
Week 0	xx (xx)	xx (xx)	xx (xx to xx)	.xx
Week 4	xx (xx)	xx (xx)	xx (xx to xx)	.xx
Week 8	xx (xx)	xx (xx)	xx (xx to xx)	.xx
Week 12	xx (xx)	xx (xx)	xx (xx to xx)	.xx
Week 16	xx (xx)	xx (xx)	xx (xx to xx)	.xx
Week 20	xx (xx)	xx (xx)	xx (xx to xx)	.xx
Week 24	xx (xx)	xx (xx)	xx (xx to xx)	.xx
Overall SZF effect				.xx
TC at	*n* = xx	*n* = xx		
Week 0	xx (xx)	xx (xx)	xx (xx to xx)	.xx
Week 12	xx (xx)	xx (xx)	xx (xx to xx)	.xx
Week 24	xx (xx)	xx (xx)	xx (xx to xx)	.xx
Overall SZF effect				.xx
TG at	*n* = xx	*n* = xx		
Week 0	xx (xx)	xx (xx)	xx (xx to xx)	.xx
Week 12	xx (xx)	xx (xx)	xx (xx to xx)	.xx
Week 24	xx (xx)	xx (xx)	xx (xx to xx)	.xx
Overall SZF effect				.xx
LDL at	*n* = xx	*n* = xx		
Week 0	xx (xx)	xx (xx)	xx (xx to xx)	.xx
Week 12	xx (xx)	xx (xx)	xx (xx to xx)	.xx
Week 24	xx (xx)	xx (xx)	xx (xx to xx)	.xx
Overall SZF effect				.xx
HDL at	*n* = xx	*n* = xx		
Week 0	xx (xx)	xx (xx)	xx (xx to xx)	.xx
Week 12	xx (xx)	xx (xx)	xx (xx to xx)	.xx
Week 24	xx (xx)	xx (xx)	xx (xx to xx)	.xx
Overall SZF effect				.xx
HbA1c at	*n* = xx	*n* = xx		
Week 0	xx (xx)	xx (xx)	xx (xx to xx)	.xx
Week 12	xx (xx)	xx (xx)	xx (xx to xx)	.xx
Week 24	xx (xx)	xx (xx)	xx (xx to xx)	.xx
Overall SZF effect				.xx
BP at	*n* = xx	*n* = xx		
Week 0	xx (xx)	xx (xx)	xx (xx to xx)	.xx
Week 4	xx (xx)	xx (xx)	xx (xx to xx)	.xx
Week 8	xx (xx)	xx (xx)	xx (xx to xx)	.xx
Week 12	xx (xx)	xx (xx)	xx (xx to xx)	.xx
Week 16	xx (xx)	xx (xx)	xx (xx to xx)	.xx
Week 20	xx (xx)	xx (xx)	xx (xx to xx)	.xx
Week 24	xx (xx)	xx (xx)	xx (xx to xx)	.xx
Overall SZF effect				.xx
ACR at	*n* = xx	*n* = xx		
Week 0	xx (xx)	xx (xx)	xx (xx to xx)	.xx
Week 4	xx (xx)	xx (xx)	xx (xx to xx)	.xx
Week 8	xx (xx)	xx (xx)	xx (xx to xx)	.xx
Week 12	xx (xx)	xx (xx)	xx (xx to xx)	.xx
Week 16	xx (xx)	xx (xx)	xx (xx to xx)	.xx
Week 20	xx (xx)	xx (xx)	xx (xx to xx)	.xx
Week 24	xx (xx)	xx (xx)	xx (xx to xx)	.xx
Overall SZF effect				.xx
ADDQoL at	*n* = xx	*n* = xx		
Week 0	xx (xx)	xx (xx)	xx (xx to xx)	.xx
Week 12	xx (xx)	xx (xx)	xx (xx to xx)	.xx
Week 24	xx (xx)	xx (xx)	xx (xx to xx)	.xx
Overall SZF effect				.xx

^a^*p* values comparing between-group differences over the entire 24-week trial

The TCM symptom and total scores will be described from the baseline to 24 weeks after medication in both groups. These symptoms include physical and mental fatigue, dry mouth and throat, lower back weakness and pain, qi deficiency, listlessness, spontaneous perspiration, night sweats, dark purplish lips, edema, and dysphoria in the chest, palms, and soles.

The improvement of TCM syndromes will be evaluated according to the symptom score method, which is conducted according to the nimodipine method [15]. Efficacy index = (score before treatment − score after treatment) /score before treatment × 100%. The criteria were as follows:

(a) *Clinical control* is defined as the resolution of most symptoms after treatment (efficacy index ≥ 95%); (b) *obvious therapeutic effect* is defined as marked improvement in most clinical symptoms (efficacy index ≥70%); (c) *with therapeutic effect* is defined as experiencing symptomatic relief (efficacy index ≥30%); (d) *invalid*: no significant improvement or symptom exacerbation (efficacy index < 30%).

Clinical efficiency will be calculated using the formula: Clinical efficiency = (clinical control case number + obvious therapeutic effect case number + with therapeutic effect number)/total number of cases × 100%.

The clinical efficiency of TCM syndrome scores after 24 weeks of treatment will be calculated for both groups (Table 6).

**Table 6 Tab6:** TCM syndrome score analysis

		SZF	SZF		Irbesartan	Irbesartan	
		Week 0	Week 24	***p*** Value	Week 0	Week 24	***p*** Value
		*n* = xx	*n* = xx		*n* = xx	*n* = xx	
Evaluation of TCM syndrome	Physical and mental fatigue	xx (xx)	xx (xx)	.xx	xx (xx)	xx (xx)	.xx
	Dry mouth and throat	xx (xx)	xx (xx)	.xx	xx (xx)	xx (xx)	.xx
	Weakness and soreness of the lower back and knees	xx (xx)	xx (xx)	.xx	xx (xx)	xx (xx)	.xx
	Qi deficiency and listlessness	xx (xx)	xx (xx)	.xx	xx (xx)	xx (xx)	.xx
	Spontaneous perspiration	xx (xx)	xx (xx)	.xx	xx (xx)	xx (xx)	.xx
	Night sweat	xx (xx)	xx (xx)	.xx	xx (xx)	xx (xx)	.xx
	Dysphoria in chest, palms, and soles	xx (xx)	xx (xx)	.xx	xx (xx)	xx (xx)	.xx
	Dark purplish lips	xx (xx)	xx (xx)	.xx	xx (xx)	xx (xx)	.xx
	Edema	xx (xx)	xx (xx)	.xx	xx (xx)	xx (xx)	.xx
Efficacy index	Clinical control	xx (xx%)	xx (xx%)	.xx	xx (xx%)	xx (xx%)	.xx
	Obvious therapeutic effect	xx (xx%)	xx (xx%)	.xx	xx (xx%)	xx (xx%)	.xx
	With therapeutic effect	xx (xx%)	xx (xx%)	.xx	xx (xx%)	xx (xx%)	.xx
	Invalid	xx (xx%)	xx (xx%)	.xx	xx (xx%)	xx (xx%)	.xx
	Overall clinical efficiency	xx (xx%)	xx (xx%)	.xx	xx (xx%)	xx (xx%)	.xx

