### Randomization and blinding

Eligible patients will be randomized in a 1:1 allocation ratio using a central permuted block randomization procedure (block size 4) with block sizes. The groups will include the TCM group, which will receive SZF and stimulated irbesartan, and the Western medicine group, which will receive SZF simulation agents and irbesartan capsules. Using the PROC PLAN process statement of SAS 9.4 (SAS/STAT Software 9.4, SAS Institute, Inc., Cary, NC, USA), a random arrangement (random coding table) of 120 subjects will be generated according to the number of seeds. The Institute of Basic Research in Clinical Medicine of the China Academy of Chinese Medical Sciences provides the random arrangement, 24-h emergency code break, and medical information. Participants, investigators, and statisticians will be blinded to treatment assignments.

SZF drugs and SZF simulators have identical shape, smell, and color, which were consistent when dissolved in water. Irbesartan capsules and simulators had consistent scent and appearance when the capsule was opened.

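### Improvement in TCM symptoms is judged by a dichotomised percent change, and no baseline-adjusted comparison of the total score is named

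*Protocol article*

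**What the plan says.** Under Secondary outcome analyses, the article sets out how this outcome is judged: "The improvement of TCM syndromes will be evaluated according to the symptom score method, which is conducted according to the nimodipine method". The efficacy index is the fall in score divided by the score before treatment. It is cut at 30, 70 and 95% into four classes, and three of them are pooled: "Clinical efficiency = (clinical control case number + obvious therapeutic effect case number + with therapeutic effect number)/total number of cases × 100" (percent). This rate is to be calculated for both groups at week 24.

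On the score itself the wording is: "The TCM symptom and total scores will be described from the baseline to 24 weeks after medication in both groups". Table 5 gives a between-arm mean difference with 95% CI for 13 of the 14 listed secondary outcomes; improvement in TCM symptoms is the one without a row. Table 6 lists nine symptoms, the four classes and the overall efficiency. It has no total-score row, and its p values are within each arm.

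Two general statements also bear on the point. The opening paragraph of Secondary outcome analyses says that changes in every secondary outcome will be compared between and within groups, and refers to Table 5. Overall principles supplies the tests: t-test or Wilcoxon for measurements, χ² or Fisher for counts, Wilcoxon for categories, a mixed model for repeated measures, and covariate adjustment where baseline is imbalanced.

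For 24-h UP the plan also has responder classes (Table 3), but beside them it fixes a full-scale analysis: "analysis of covariance (ANCOVA) will be performed to analyze the 24-h UP change from baseline to week 24, using baseline 24-h UP as a covariate".

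**The concern.** A multi-symptom score with a total is reduced first to a percentage of own baseline, then to four classes, then to two. In the final rate a patient who improves by 31% counts the same as one who improves by 90%, and a patient who improves by 29% counts the same as one who worsens. The index also depends on where the patient starts: a fall from 20 to 15 is 5/20 = 25% and fails, while a fall from 3 to 2 is 1/3 = 33% and passes.

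With at most 60 patients per arm, a real difference in symptoms between SZF and irbesartan is then easier to miss. The effective rate also reflects where the arms sit relative to the 30% line as well as how much symptoms changed. A more precise analysis of data already collected is available, and the plan uses it for 24-h UP, but it is not named here.

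**Working it through.** **No figure to reproduce.** The article states no power, effect size, SD, correlation or response rate for the TCM score, and refers to the earlier protocol for the sample size.

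**Inputs from the article**
- Test level: "all the statistical analysis tests will use two-sided tests with a nominal alpha level of 0.05" (Overall principles).
- Size: "A total of 120 patients with DKD will be equally and randomly divided into two groups" (abstract), and "Eligible patients will be randomized in a 1:1 allocation ratio" (Randomization and blinding), so 60 per arm.
- Cuts on the efficacy index: 30, 70 and 95%; effective means at least 30%.

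**Inputs assumed:** baseline total mean 16, SD 5; arm difference d = 0.4 or 0.5 SD; correlation ρ between baseline and week 24 of 0.3, 0.5 or 0.7; mean reduction in the control arm of 15 to 60%.

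**Check by formula** (d = 0.5, n = 60 per arm)
- ANCOVA power = Φ(d/√(1−ρ²) × √(n/2) − 1.96). At ρ = 0.5: 0.5/0.866 × 5.477 = 3.162, and Φ(1.202) = 0.885. At ρ = 0: 0.5 × 5.477 = 2.739, and Φ(0.779) = 0.782.
- The same normal score cut so that 50% of controls respond: the other arm has Φ(0 + 0.5) = 69.1%, and two-proportion power is 0.57. Over control rates of 30 to 60% it is 0.54 to 0.58.
- Loss: from 0.78 − 0.58 = 20 points to 0.885 − 0.54 = about 35 points.

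This formula cuts the week-24 score. The plan cuts the percent change, which already uses some baseline information, so simulation is closer to the plan.

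**Check by simulation** (1,500 trials per row, integer scores, standard error of each power at most √(0.25/1500) = 1.3 points). Power in %, d = 0.5, 60 per arm:

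| ρ | Mean control reduction | Control effective rate | ANCOVA | Change-score t-test | Four classes, Wilcoxon | Yes/no, χ² |
|---|---|---|---|---|---|---|
| 0.3 | 15% | 32% | 79.9 | 62.3 | 58.5 | 55.5 |
| 0.3 | 30% | 50% | 81.6 | 64.3 | 68.4 | 56.9 |
| 0.3 | 45% | 68% | 79.9 | 60.1 | 71.3 | 47.8 |
| 0.3 | 60% | 83% | 76.5 | 57.3 | 71.9 | 33.9 |
| 0.5 | 15% | 30% | 88.5 | 77.3 | 72.2 | 69.5 |
| 0.5 | 30% | 50% | 87.8 | 77.6 | 76.7 | 67.4 |
| 0.5 | 45% | 71% | 87.6 | 75.7 | 79.8 | 59.2 |
| 0.5 | 60% | 86% | 84.0 | 68.3 | 77.7 | 40.5 |
| 0.7 | 15% | 26% | 96.1 | 93.1 | 86.6 | 84.3 |
| 0.7 | 30% | 51% | 96.0 | 92.5 | 88.0 | 82.3 |
| 0.7 | 45% | 75% | 95.9 | 91.1 | 86.5 | 69.0 |
| 0.7 | 60% | 91% | 94.8 | 87.3 | 82.0 | 38.1 |

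Taking these rows together with those at d = 0.4:
- **Yes/no rate against ANCOVA**, control rates of about 25 to 75%: loss from 96.1 − 84.3 = 12 points to 79.9 − 47.8 = 32 points. Where ANCOVA has 80 to 89% power, the loss is about 18 to 32 points; the smallest losses arise where ANCOVA is already at 96%. At control rates of 82 to 91% the loss is 33 to 57 points.
- **Four classes against ANCOVA:** loss from 76.5 − 71.9 = 5 points to 79.9 − 58.5 = 21 points.
- **Yes/no rate against an unadjusted change-score t-test**, control rates up to 75%: loss of about 6 to 25 points.
- **Four classes against that same t-test:** from about 12 points worse to 16 points better, close to zero on average.
- **At 50 per arm**, the yes/no rate loses about 16 to 31 points against ANCOVA at control rates up to 75%, and 27 to 58 above that.

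A second set of 27 scenarios (baseline mean 10 to 15, SD 4 to 5, same correlations, control improvement 20 to 45%, effect set for about 79% ANCOVA power) gave losses of 15 to 32 points for the yes/no rate and 6 to 18 for the four classes. Against the change-score t-test, the yes/no rate lost 5 to 24.

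**The case against.** A reader might infer that the cut is the only analysis of this outcome. The article does not support that. Its general sentence on comparing all secondary outcomes covers TCM symptoms, Overall principles supplies a test for a continuous measure, and being described does not exclude being compared: 24-h UP is also to be described, and is then compared. This stands. But that sentence refers to Table 5, which omits TCM; Table 6 has no place for a total or for a between-arm result; and the default test is unadjusted unless baseline is imbalanced. Two possible analyses are left, with neither named as the main one.

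It is also fair that part of the loss against ANCOVA is missing baseline adjustment. ANCOVA with the baseline value is named for 24-h UP alone, so no secondary outcome has it by default. Against the plan's own unadjusted continuous test, the four classes cost little on average. What remains is the pooled rate, which loses power even against that test.

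The fall from 3 to 2 is only an illustration, because the article gives neither the item scale nor any minimum score at entry. The index follows a cited scoring method that is not at hand, and preferring a responder rate for a symptom outcome is partly a matter of custom. Neither point requires the rate to be the main between-arm analysis.

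**Conclusion.** The point holds for a secondary outcome. The plan evaluates improvement in TCM symptoms on a cut scale, names no baseline-adjusted analysis of the total score, and gives that score no place in its tables.

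A single figure, such as 15 to 30 points of lost power, would be tempting but is not supported as a fact about this trial: every input on the TCM score is assumed, and such a figure would apply to the pooled yes/no rate only. Under the stated assumptions the loss against ANCOVA is roughly 12 to 32 points for the yes/no rate at control effective rates of 25 to 75%, larger at higher rates, and about 5 to 21 points for the four ordered classes. Against an unadjusted change-score t-test it is about 5 to 25 points for the yes/no rate. Nor does the point touch the primary comparison or its power.

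**What to change.** By a dated amendment before unblinding, name as the main between-arm analysis of this outcome an ANCOVA of the week-24 total TCM symptom score with the baseline total as covariate. Report the adjusted SZF minus irbesartan difference with its 95% CI, and add a total-score row for it in Table 5 or Table 6. Keep the four classes and clinical efficiency as supportive results.

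No new data are needed. The costs are small but real. The customary efficiency rate is no longer the headline for this outcome. The amendment would also come after the September 2018 interim analysis, which was planned to cover secondary outcomes, so it should be written by people who have not seen the interim results and should say so.
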